### Sample size

A large population-based study using the UK General Practice Research Database found that true complications occurred in 17.6% of at-risk children aged 1–14 years within 30 days of being clinically diagnosed with influenza/ILI.^23^ Assuming that true complications account for 44% of reconsultations due to clinical deterioration,^24^ we estimate that 40% (17.6%/44×100) of at-risk children with clinical influenza will reconsult with clinical deterioration within 30 days of initial presentation.

We will aim to recruit 650 children into the trial, including an inflation factor of 1.041 and allowance for 25% loss to follow-up. Our target effective sample size is therefore 484 children (242 in each arm), which would be sufficient to detect a reduction in reconsultation due to clinical deterioration from 40% to 26% (a 35% relative risk reduction) with 90% power and 5% two-tailed alpha error. Our inflation factor estimate is based on a conservative intracluster correlation estimate of 0.03^25^ and a coefficient of variation of 0.6 (based on the value observed in the Diabetes care from Diagnosis (DD) trial),^26^ assuming an average cluster size of two patients.^27^

We acknowledge that recruitment of the above sample size is likely to be challenging (see Discussion). However, a sample of 280 participants would still be sufficient to detect a reduction in reconsultation due to clinical deterioration from 40% to 23% with 80% power and 5% two-tailed alpha error, including an inflation factor of 1.041 and allowance for 5% loss to follow-up. This effect size (a 42.5% relative risk reduction) is still conservative compared with the effect observed in the aforementioned trial conducted by Maeda *et al*,^15^ which reported an 85% relative risk reduction in incidence of pneumonia in children with ILI who were treated with the antibiotic sultamicillin (1/42 children) versus placebo (7/43 children). A 5% loss to follow-up rate should also be achievable given that data on reconsultations due to clinical deterioration will be extracted from medical notes.

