## Discussion

### Implications of study findings

The findings of the ARCHIE trial will provide important evidence to inform clinically appropriate and cost-effective antibiotic prescribing and use in ‘at risk’ children presenting with ILI in community healthcare settings. The only randomised placebo-controlled trial conducted to date of early antibiotic use in children with ILI^15^ excluded children with chronic medical conditions (even though these children are at greatest risk of clinical deterioration) and did not evaluate potential implications of antibiotic treatment on antimicrobial resistance. There are also no studies to date that have examined the cost-effectiveness, costs and effectiveness of early antibiotic use in ‘at risk’ children with influenza/ILI.

The lack of clear, evidence-based guidance in this area results in considerable uncertainty and wide variation in clinical decision making about prescribing antibiotics to children with ILI who have known risk factors for influenza-related clinical deterioration.^30^ This may in turn result in antibiotics being prescribed unnecessarily, leading to emergence of antibiotic-resistant infections,^31^ which are associated with worse clinical prognosis, even in patients with common respiratory tract infections in the community.^32^

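### The fallback effect of a 42.5% relative reduction is called conservative on the strength of a pneumonia result, which does not support that description; power at 280 for the planned 35% effect is not given.

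*Protocol article*

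**What the plan says.** The Sample size section derives the control rate in two steps. It reports that "true complications occurred in 17.6% of at-risk children". It then continues: "Assuming that true complications account for 44% of reconsultations due to clinical deterioration", and concludes: "we estimate that 40% (17.6%/44×100) of at-risk children with clinical influenza will reconsult with clinical deterioration". The main design aims for 650 children and a fall from 40% to 26%, a 35% relative reduction, with 90% power.

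The section then concedes that recruiting 650 will be hard and offers a fallback: "a sample of 280 participants would still be sufficient to detect a reduction in reconsultation" "from 40% to 23% with 80% power and 5% two-tailed alpha error", "including an inflation factor of 1.041 and allowance for 5% loss to follow-up". The size of the fallback effect has one justification: "This effect size (a 42.5% relative risk reduction) is still conservative compared with the effect observed in the aforementioned trial". That trial is described as showing an 85% relative reduction in pneumonia, 1/42 on the antibiotic against 7/43 on placebo. The Discussion (Implications of study findings) adds that the same trial "excluded children with chronic medical conditions (even though these children are at greatest risk of clinical deterioration".

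The Outcomes section defines the primary outcome more widely than complications: worsening symptoms and new symptoms also count.

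**The concern.** The comparison sets a relative reduction in one endpoint against a relative reduction in another. Pneumonia is a single complication. Reconsultation for deterioration is a broad outcome, and the article takes less than half of it to be true complications. A large effect on the narrow part becomes a smaller effect on the whole unless the rest also falls. The article had the conversion figure, 44%, and used it for the control rate but not for the effect size.

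The fallback also replaces the planned effect with a larger one. A reader sees 80% power for an effect described as cautious and is not told what 280 participants offer for the effect the trial was designed to detect. This matters because the Reflection section reports the final recruitment season with recruitment harder than expected.

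**Working it through.** **Inputs** (Sample size section): control rate 40%; true complications 17.6%, or 44% of reconsultations; fallback 40% v 23%, 80% power, two-sided 5%, inflation factor 1.041, 5% loss, total 280; planned effect 40% v 26%; benchmark 1/42 v 7/43. Equal allocation is assumed for the fallback, as in the main design.

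**1. Reproduce the 280.** Per arm, n = [1.96·√(2p̄(1−p̄)) + 0.8416·√(p₁(1−p₁) + p₂(1−p₂))]² / d².
- With p₁ = 0.40, p₂ = 0.23, p̄ = 0.315 and d = 0.17: (1.2876 + 0.5435)² / 0.0289 = 116.0, so 117 per arm and 234 in total. Then 234 × 1.041 / 0.95 = 256.4, or 257.
- With continuity correction, n′ = (n/4)[1 + √(1 + 4/(nd))]² = 127.5, so 128 per arm and 256 in total. Then 256 × 1.041 / 0.95 = 280.5.

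The stated 280 therefore matches the continuity-corrected formula.

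**2. Power at 280.** Effective number per arm: 280 × 0.95 / 1.041 / 2 = 127.8. Uncorrected power is Φ{[d√n − 1.96·√(2p̄(1−p̄))] / √(p₁(1−p₁) + p₂(1−p₂))}. Corrected power uses the n for which n′ = 127.8.

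| Comparison | Relative reduction | Corrected | Uncorrected |
|---|---|---|---|
| 40% v 23% (fallback) | 42.5% | 80% | 84% |
| 40% v 25% (benchmark translated, step 3) | about 37% | 68% | 73% |
| 40% v 26% (planned effect) | 35% | 61% | 66% |

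The first row confirms the article's 80%. The last row needs no assumption about how the drug works. For example, uncorrected: (0.14 × √127.8 − 1.3034) / 0.6576 = 0.424, and Φ(0.424) = 0.66.

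**3. Put the benchmark on the reconsultation scale.** Assume that the antibiotic prevents true complications and leaves other reconsultations unchanged. Assume also that the 85% seen for pneumonia applies to every complication.
- Benchmark: 0.85 × 17.6 = 14.96 points, so 40% falls to 25.04%. Relative reduction: 14.96 / 40 = 37.4%.
- Fallback: 17.0 / 17.6 = 96.6% of complications would have to be prevented.
- Planned effect: 14.0 / 17.6 = 79.5%, which is below 85%. The objection is therefore specific to the fallback.

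**4. Relax the complications-only assumption.** Other reconsultations make up 40 − 17.6 = 22.4 points. With 85% of complications prevented, reaching 23% needs a further 25.04 − 23 = 2.04 points, and 2.04 / 22.4 = 9.1% of other reconsultations.

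**5. Precision of the benchmark.** RR = (1/42) / (7/43) = 0.146. SE of log RR = √(1 − 1/42 + 1/7 − 1/43) = 1.047. The Wald 95% CI is exp(−1.922 ± 1.96 × 1.047), about 0.02 to 1.14. Fisher's exact p = 0.058.

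**The case against.** The best defence is that the article makes no false calculation and hides little. The 80% power is stated for 40% v 23% and reproduces. The 35% and 42.5% appear in consecutive paragraphs, the comparator endpoint is named, and its counts are given. The word conservative is tied to one comparison. All of this stands, so the point concerns justification and omits any charge of wrong arithmetic.

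Three stronger readings are tempting and are not supported.
- A reader might infer that 44% is a hard upper limit on the reduction in reconsultation. The article uses 44% only to obtain the control rate and does not say that the drug acts solely through complications. The outcome includes worsening and new symptoms, and Background and rationale cites observational data on shorter fever with early antibiotics. Step 4 shows that a modest effect on other reconsultations would be enough to pass the translated benchmark.
- A reader might infer that a trial of 280 is much weaker than stated. It is not weaker for the effect stated. It has less power for smaller effects, about which the article says nothing.
- A reader might infer that 650 has been given up and that 280 is the new target. The article says only that 650 will be challenging.

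The exclusion of children with chronic conditions shows that the benchmark comes from a different population. It does not show in which direction the effect would differ.

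The defence does not rescue the word itself. Even with benefit beyond complications, 42.5% needs the full benchmark effect on all complications plus something more, or a still larger effect elsewhere. The article does not argue for either.

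**Conclusion.** The description of the fallback effect as conservative is unsupported. Two facts rest on no assumption about mechanism: 42.5% exceeds the planned 35%, and power at 280 for the planned effect is about 61% (66% uncorrected), against 90% in the main design. One conclusion is conditional. If benefit comes only through true complications, the fallback is more optimistic than its own benchmark (42.5% against about 37%), and power at the translated benchmark is about 68% (73% uncorrected). The benchmark is also too imprecise, at 8 events with an interval that includes no effect, to make another effect look cautious. The 280, the 80% power for 40% v 23% and the main design are unaffected by this point.

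**What to change.** In the Sample size section:
- Delete the statement that the fallback effect is conservative, together with the pneumonia comparison.
- State that the 42.5% reduction is larger than the planned 35%.
- State the power of 280 for the planned 40% v 26% as about 61% on the continuity-corrected formula that yields 280 (66% uncorrected), and for 40% v 25% as about 68% (73% uncorrected). Name the formula, so that figures from the two are not mixed beside the stated 80%.
- If benefit beyond complications is expected, say so and give the size assumed. With 85% of complications prevented, about a 9% fall in other reconsultations is what the fallback requires.

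The cost is a less favourable stated power. No extra patients are needed, and neither the endpoint nor the primary analysis changes.

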### Statistical analysis and economic evaluation plan

We will perform an intention-to-treat analysis including all randomised participants and use multiple imputation methods to account for missing data. Specifically, the participants will be analysed in the groups to which they were allocated. Baseline characteristics will be summarised by treatment groups. The results from the trial will be presented as comparative summary statistics (difference in proportion or means) with 95% CIs. The analysis and reporting of results will follow the general principles of Consolidated Standards of Reporting Trials 2010 statement.^28^

The proportion of children reconsulting due to clinical deterioration in the two groups (primary outcome) will be compared using a log-binomial regression model with adjustment for region, age and seasonal influenza vaccination status. The treatment effect will be reported as a relative risk with 95% CI. A p value will also be presented. Stability and assumptions of the regression model will be explored, and alternative method will be used if any violation of assumptions occurred.

Analysis of continuous outcomes (eg, duration of fever and duration of symptoms) will be compared using regression analysis, adjusting for the same factors as described above. A non-parametric method will be used if assumptions of linear regression are not met. Binary outcomes (eg, proportions of children prescribed medication and/or requiring further investigations, children in whom adverse events are reported and children who are hospitalised or died within 28 days of randomisation) will be compared using χ^2^/Fisher’s exact test and log-binomial regression. Sensitivity analyses will be carried out to examine the robustness of the results with different assumptions about departures from randomisation policies and handling of missing data.

The incremental costs of administering early treatment with co-amoxiclav in ‘at risk’ children with influenza/ILI versus placebo will be estimated using the data on healthcare resource use provided by the four 1-week study diaries and the medical notes review. We will estimate total costs and costs relating to burden on primary care, secondary care and parental/informal care. We will extrapolate our analysis of resource use and costs to explore the potential cost impact of early co-amoxiclav use on a national scale. The primary outcome measure for the cost-effectiveness analysis will be the EQ-5D-Y proxy. We will estimate and report all the costs and consequences in a disaggregated format (cost–consequences analysis) as well as analysing and reporting the incremental cost and effectiveness in terms of cost per quality-adjusted life year of administering co-amoxiclav versus placebo alongside a sensitivity analysis.

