**Methods and analysis:**

The ARCHIE trial is a double-blind, parallel, randomised, placebo-controlled trial. ‘At risk’ children aged 6 months to 12 years inclusive who present within the first 5 days of an ILI episode will be randomised to receive a 5-day course of oral co-amoxiclav 400/57 twice daily or placebo. Randomisation will use a non-deterministic minimisation algorithm to balance age and seasonal influenza vaccination status.

To detect respiratory virus infections, a nasal swab will be obtained from each participant before commencing study medication. To identify carriage of potential bacterial respiratory pathogens, we will also obtain a throat swab where possible.

The primary outcome is reconsultation in any healthcare setting due to clinical deterioration within 28 days of randomisation. We will analyse this outcome using log-binomial regression model adjusted for region, age and seasonal influenza vaccination status.

Secondary outcomes include duration of fever, duration of symptoms and adverse events. Continuous outcomes will be compared using regression analysis (or equivalent non-parametric method for non-normal data) adjusting for minimisation variables. Binary outcomes will be compared using χ^2^/Fisher’s exact test and log-binomial regression.

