Box 2Study inclusion and exclusion criteriaInclusion criteriaAged 6 months–12 years inclusive.In ‘at risk’ category.Presenting with influenza-like illness (ie, cough and fever) during influenza season.Presenting within 5 days of symptom onset.Permanently registered at a general practice in UK.Parent/guardian able to complete study diary and questionnaires.Exclusion criteriaThe participant may not enter the trial if ANY of the following apply:Known contraindication to co-amoxiclav.Child given antibiotics for treatment of an acute infection within the last 72 hours.Child requires immediate antibiotics (clinician’s judgement).Child requires immediate hospital admission for treatment of an influenza-related complication (clinician’s judgement).Child has been observed on hospital ward or ambulatory care unit for longer than 24 hours.Presence of any reason to prevent healthcare professional from obtaining nasal swab.Child with known cystic fibrosis.Child previously entered into the Antibiotics for at Risk CHildren with InfluEnza trial.Child has been involved in another medicinal trial within the last 90 days.

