### Baseline study procedures

Healthcare professionals will record baseline data from study participants on age, sex, comorbidities, household smoking status, influenza vaccination status, medications given during the current illness episode, duration of fever and duration of symptoms. Heart rate and respiratory rate will also be measured and recorded at baseline. Other baseline characteristics (medical conditions, regular medications, vaccinations and acute consultations that occurred up to 12 months before randomisation) will be extracted from participants’ medical records.

A nasal swab will be obtained from each participant at baseline. Nasal swabs will be placed in viral transport medium and sent by post to Alder Hey Children’s Hospital microbiology department for analysis, where they will be analysed by real-time PCR analysis to detect influenza and distinguish influenza A, B and A/H1N1 2009 pandemic subtypes. Residual medium will be retained for potential future detection of other pathogens. Where possible, a throat swab will also be obtained from the participant for culture and sensitivity. In a subgroup of participants whose parents/guardians give additional written informed consent, further throat swabs will be collected after 3, 6 and 12 months. Online supplementary appendix A provides further details of the laboratory analyses, which will be performed on throat swab samples.

10.1136/bmjopen-2017-021144.supp1Supplementary data

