### Outcomes

The primary outcome is reconsultation due to clinical deterioration within 28 days of randomisation. Clinical deterioration is defined as any of: worsening symptoms, development of new symptoms or development of a complication requiring medication or hospitalisation. This definition is based on that used by the Genomics to combat Resistance against Antibiotics in Community-acquired lower respiratory tract infection in Europe consortium in order to define reconsultations due to clinical deterioration in patients with lower respiratory tract infections.^22^

Secondary outcomes include duration of fever and duration of symptoms from time of randomisation and medication prescriptions and/or further investigations, adverse events, hospitalisations or deaths, all within 28 days of randomisation. For the purpose of the economic evaluation, outcomes include healthcare resource utilisation and parental/informal care costs within 28 days of randomisation and health-related quality of life as measured by the EuroQol health-related quality of life youth proxy version (EQ-5D-Y proxy) at baseline and days 4, 7, 14 and 28.

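### Baseline duration of fever and of symptoms is recorded but is not a named covariate for the two duration outcomes; pre-specifying it costs almost nothing and may gain precision

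*Protocol article*

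**What the plan says.** All references are to the protocol article.

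- **Baseline study procedures.** Healthcare professionals record, among other items, "medications given during the current illness episode, duration of fever and duration of symptoms".
- **Outcomes.** The secondary outcomes include "duration of fever and duration of symptoms from time of randomisation". The time before randomisation is therefore not part of the outcome.
- **Study participants, Box 2.** Entry requires "Presenting within 5 days of symptom onset".
- **Statistical analysis and economic evaluation plan.** The primary outcome uses a "log-binomial regression model with adjustment for region, age and seasonal influenza vaccination status". Continuous outcomes, with the two durations given as the examples, are analysed by regression "adjusting for the same factors as described above". The section adds: "A non-parametric method will be used if assumptions of linear regression are not met". It does not say whether that method would keep the covariates.
- **Abstract, Methods and analysis.** Continuous outcomes are compared "adjusting for minimisation variables". Here too no baseline duration is named.

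**The concern.** Two children can enter the trial at quite different stages of the same kind of illness, one on the first day and one on the fifth. The outcome clock starts at randomisation for both. Time already spent ill is thus a natural candidate to explain some of the spread in remaining duration. Region, age group and vaccination status do not measure it, and the randomisation does not balance it by design.

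The baseline value of each outcome's own quantity is in hand, yet the article names a covariate set without it. If it is prognostic, the confidence intervals for two stated trial objectives (shorter fever, shorter symptoms) will be wider than they need be. Naming the covariate in advance matters because adding it after an imbalance has been seen would look driven by the data.

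**Working it through.** **The plan's own figures.** No effect size, standard deviation, correlation or power is stated for either duration outcome, so there is no figure for them to reproduce. The Sample size section concerns the primary outcome only (40% v 26%, "with 90% power and 5% two-tailed alpha error"). It reproduces:

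- Mean proportion = (0.40 + 0.26)/2 = 0.33.
- n per arm = [1.96 × √(2 × 0.33 × 0.67) + 1.2816 × √(0.40 × 0.60 + 0.26 × 0.74)]² / 0.14² = 235.
- 2 × 235 × 1.041 / 0.75 = 652, against 650 stated.

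This serves only to set plausible analysis sizes: the effective target of 484, and 280 × 0.95 = 266 under the stated smaller scenario.

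**Is the covariate legitimate?** Yes. It is recorded at baseline and, by the Outcomes section, does not overlap with the outcome.

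**Gain if it is added.** In a linear model, adding one baseline covariate multiplies the standard error (SE) of the treatment effect by √(1 − r²). Here r is the partial correlation between baseline duration and outcome, given the covariates already in the model. The equivalent gain in sample size is 1/(1 − r²) − 1. The last column shows what a comparison with 80% power would become: Φ[(1.96 + 0.8416)/√(1 − r²) − 1.96]. The 80% is an illustrative starting point. The values of r are assumptions.

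| r (assumed) | SE ratio | Equivalent gain in sample size | Power, from 80% |
|---|---|---|---|
| 0 | 1.000 | 0% | 80.0% |
| 0.1 | 0.995 | 1.0% | 80.4% |
| 0.2 | 0.980 | 4.2% | 81.6% |
| 0.3 | 0.954 | 9.9% | 83.6% |
| 0.4 | 0.917 | 19.0% | 86.4% |
| 0.5 | 0.866 | 33.3% | 89.9% |

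**Cost if it is useless (r = 0).** One residual degree of freedom is lost. Take seven parameters before and eight after (an assumption, since the number of regions is not given):

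- N = 484: √(477/476) = 1.001, an SE increase of about 0.1%.
- N = 266: √(259/258) = 1.002, about 0.2%.

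More regions hardly change this: with 27 and 28 parameters at N = 266, √(239/238) = 1.002.

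**Check by simulation.** The setting was a right-skewed outcome, a covariate limited to 0 to 5 whole days, no treatment effect, and 2000 runs per case at N = 266 and N = 484. The ratio of the adjusted to the unadjusted standard deviation of the estimate was 1.002 at r = 0, 0.954 to 0.962 at r = 0.3, and 0.870 to 0.877 at r = 0.5. This is close to the formula. Neither analysis showed bias.

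**The case against.** The plan adjusts for every factor used in the randomisation, which is a standard and coherent rule. The estimates are valid under randomisation without baseline duration. A full analysis plan may add prognostic covariates for secondary outcomes. The first two points stand. The third does so only in part: the article does not stay silent but names the covariates for exactly these two outcomes, so the omission is what the text currently fixes.

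Several stronger readings are tempting, and the article supports none of them.

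- **Remaining duration depends strongly on illness day, so precision is certainly being lost.** No correlation is given. Entry within five days narrows the covariate. Fever may be child- or parent-reported, so its earlier duration may be imprecise. Even the sign is unclear: a longer illness so far may mean less to come or may mark a more persistent illness, and the two could partly cancel. At r = 0.5 the covariate explains 25% of the remaining variance; at r = 0.3, 9%.
- **A chance imbalance in illness day would bias the result.** The planned confidence interval already allows for chance imbalance. If entry were uniform over 0 to 5 days (assumed, SD 5/√12 = 1.44) with 133 analysed per arm, the standard error of the between-arm difference in illness day would be 1.44 × √(2/133) = 0.18 days.
- **The trial will probably analyse about 280 children.** The article keeps 650 as its target and gives 280 as a smaller size that would still suffice for the primary outcome, while acknowledging difficult recruitment. The 5% loss assumed there rests on extraction from medical notes. The durations come from parent diaries, with telephone calls added for fever, so that rate does not carry over to them.

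A last objection stands and shapes the fix: the tabulated gain belongs to the linear model. Durations are often skewed, and a plain rank test in its place would use no covariate at all.

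**Conclusion.** The point holds as an inexpensive improvement, not as an error. Both baseline durations are collected, both are proper covariates, and the named covariate set omits them. The planned estimates remain unbiased. Only two secondary outcomes are affected; the primary outcome, its model and its sample size are not.

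The size is unknown because r is unknown. Over r = 0 to 0.5 the equivalent gain in sample size runs from 0% to 33%. It is slight up to about r = 0.2 (4%) and worth having from about r = 0.3 (10%). Against this stands a cost in standard error of about 0.1 to 0.2% if r is zero. These figures assume a linear model with baseline duration entered as a linear term. With almost no downside and a possible material gain, adding the covariate is the better choice whatever r turns out to be.

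**What to change.** Before unblinding, state in the analysis plan that:

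1. the fever-duration model includes duration of fever before randomisation as a continuous covariate, beside region, age and vaccination status;
2. the symptom-duration model likewise includes duration of symptoms before randomisation;
3. if the assumptions of linear regression fail, the method that replaces it keeps the same adjustment.

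This takes a few lines of wording and one degree of freedom per model. It needs no new data and no change to recruitment, follow-up or the primary analysis.
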